## Abstract

**Background:**

Trauma-related disorders and personality disorders are prevalent in survivors of chronic childhood trauma and neglect. Both conditions have serious consequences for patients, their families, society and public health and a high risk of development of chronicity. However, information on the long term course trajectories is lacking and predictors of course outcome in survivors of chronic childhood traumatization are unknown. The first aim of the current study is to identify two-year course trajectories of pathology in patients with trauma-related disorders and personality disorders. The second aim is to examine predictors of the course, including demographics, clinical characteristics and comorbidities.

**Methods/design:**

The study is a naturalistic two-year follow-up of 150 patients consecutively admitted to the trauma treatment program and the personality disorder treatment program respectively at GGZ Friesland, a regular Dutch mental health care center. The only exclusion criterion is insufficient mastery of the Dutch language. Participants will be assessed after 2 years of treatment through measures that have been completed at baseline, including structured clinical interviews to measure childhood histories of trauma and neglect, (symptoms of) trauma-related disorders and personality disorders, and psychological questionnaire measures (e.g., general psychopathology, depressive symptoms and personality features). In addition, participants will complete an evaluation questionnaire to assess medication prescribed and treatment (s) received outside GGZ Friesland between baseline and follow-up. Information about (psychological and pharmacological) treatment received at GGZ Friesland during the follow-up period will be collected from patient files.

**Discussion:**

This study provides insight in the two-year course of (comorbid) trauma-related disorders and personality disorders. Identifying predictors of the course of trauma-related and personality disorders will allow to differentiate clinical profiles and will offer indicators for treatment.

## Background

Personality disorders and trauma-related disorders are associated with significant personal and societal burden, largely because of the development of chronicity and public health consequences [1, 2]. Though prevalent and impairing conditions, data on the long-term prognosis (course) of trauma-related disorders and personality disorders are scarce, in particular among survivors of chronic childhood traumatization. The available data suggest that both groups of disorders tend to run a chronic course. However, most studies tend to focus on the naturalistic short-term course of the disorders and do not focus on the (course of the) comorbidity between both categories of disorders, e.g. [3–5].

With regard to trauma-related disorders, there are several studies focusing on the natural course of posttraumatic stress symptoms or disorder (PTSD) [3, 4]. Many, if not most of these studies focusing on course of PTSD make no clear distinction between the type of trauma (simple or chronic, interpersonal or not), nor between the onset of trauma (in childhood or adulthood). A recent review concludes that trajectories of PTSD after intentional traumatic experience, i.e. deliberate infliction of harm, show wide variability: among the patients who develop PTSD, one third remit within 3 months, while in nearly 40% of cases PTSD may become chronic. This review also notices that only a few studies between 1998 and 2010 have followed participants for more than a year [5]. One of these studies [3] with a longer (i.e. 5 year) follow-up among patients with anxiety disorders shows that PTSD is a persistent illness. Another important result of this study is that trauma in childhood, compared with trauma in adulthood, predicts a longer time to remit from chronic PTSD, especially in case of comorbidity with Borderline Personality Disorder (BPD). Also, a later study found that childhood sexual abuse (CSA) predicts less improvement of PTSD symptomatology when comorbid with BPD [6]. However, a study among veterans receiving inpatient treatment for PTSD indicates that a history of childhood trauma (i.e. physical or sexual abuse, or witnessing family violence or deaths before age 7) does not predict a less favourable short-term course of PTSD symptoms, but rather the severity or complexity of the trauma-related symptoms, i.e. the presence of complex PTSD (here formulated as Disorder of Extreme Stress Not Otherwise Specified (DESNOS)) [7]. Affect dysregulation is a pervasive symptom in survivors of childhood trauma, associated with both trauma-related disorders and personality disorders [8, 9]. Although some studies did measure affect dysregulation as a symptom of complex PTSD [10], there are no studies known to specifically report data on the course of affect dysregulation.

Regarding clinical complexity, a recent meta-analysis [11] reports a comorbidity rate of any personality disorder for PTSD of 35%. This meta-analysis shows that PTSD is clinically heterogeneous, implying that, compared to all other anxiety disorders, PTSD has a highly different comorbidity profile with a mixture of personality disorder comorbidity. It suggests that the heterogeneity in clinical profile may be explained by a large variety in nature and impact of traumatic exposures. Furthermore, (cumulative) trauma during developmental years predicts increasing symptom complexity in adults, whereas adulthood trauma does not [12].

Several studies focusing on PTSD and comorbid dissociative symptoms among early traumatized patients indicate that higher levels of dissociative symptoms are accompanied by higher levels of PTSD symptoms, while the level of dissociation based on self-report (DES) does not seem to influence the course of symptoms of PTSD during treatment [10, 13]. A naturalistic 12-month post-treatment follow-up study of early traumatized inpatients with PTSD found that patients with a co-occurring complex dissociative disorder, i.e. dissociative identity disorder (DID) and dissociative disorder not otherwise specified with clinical features of DID (DD NOS-1), need more time to improve on dissociation, symptoms of PTSD, depression, general psychiatric symptoms and interpersonal functioning, compared to patients without these co-occurring disorders [14]. Recently, a study on the two-year course of post-traumatic stress symptoms and dissociative symptoms in female survivors of childhood abuse, who received 6 weeks of inpatient treatment, reports significant improvement of the global symptom load, PTSD symptoms and depressive symptoms, but no significant improvements concerning dissociative symptoms [15]. Although a group was identified which remained stable or improved during the follow-up period, no significant predictors of course outcome were found.

Study findings on the course of personality disorders suggest that even severe personality disorders can improve significantly within a couple of years, with the majority of the studies concerning BPD [16–19]. Two longitudinal studies, the Collaborative Longitudinal Personality Disorder Study (CLPS) [20, 21] and the McLean Study of Adult Development (MSAD) [22], focus on identifying features that influence the course of several personality disorders. Both studies conclude that a history of trauma or neglect predicts a more negative course of BPD. The CLPS also reports that patients with either schizotypical personality disorder or BPD had experienced higher rates of being physically attacked and reported more types of traumatic exposure. Furthermore, the CLPS finds that the severity of personality psychopathology, i.e. the number of criteria met, and a low score on the Global Assessment of Functioning (GAF), have a negative influence on the course of BPD after 2 years of treatment [20]. The MSAD, focusing on a longer (10-year) course of borderline personality disorder, finds that a younger age, no history of childhood sexual abuse, less severe childhood abuse and neglect, less severe violence witnessed as a child, no prior psychiatric hospitalization, absence of PTSD and anxious cluster personality disorders, as well as four facets of normal personality (low neuroticism and high extroversion, agreeableness and conscientiousness) predict an earlier time to remission of the BPD, when measured every 2 years [22].

Although many studies have focused on describing the comorbidity between trauma, trauma-related disorders and personality disorders [23], little research has been done on the long term course of these comorbidities. This lack of information is due to methodological limitations of previous studies, like short term follow-up [7, 14], using only (self-report) symptom questionnaires [10, 13, 15], and, concerning (comorbidity of) personality disorders, focussing only on specific disorders, like BPD [19, 20]. We designed the present study to overcome these limitations of the previous studies and expect therefore to be better able to identify predictors of two-year course outcome. Furthermore, the present study will test a theoretical model of Draijer [23, 24], while previous studies lack a theoretical background. We use the diagnostic square of Draijer (see Fig. 1) to study the (comorbid) course of trauma-related disorders and personality disorders. This two-dimensional diagnostic model accounts for the influence of trauma and neglect on the development of (the spectrum of) trauma-related disorders as well as personality disorders. The severity of trauma endured, as the first dimension, situated on the y-axis, fluctuates depending on factors such as the age on which the trauma occurred, how frequently it occurred and the relationship to the perpetrator. This dimension is assumed to be related to the severity of trauma-related disorders. Situated on the x-axis, the severity of emotional neglect represents the second dimension. This dimension is assumed to be related to the severity of personality disorders. Thus a square is created, that gives an indication on the treatability of these disorders by psychotherapy, with highly treatable psychopathology on the low end of the dimensions, and highly untreatable psychopathology on the high end of the dimensions [24]. While this model already has shown its relevance in clinical practice as a diagnostic model, the aim of this study is to test if it can be validated as a prognostic model for course of illness: will it be affected by characteristics of the patient, treatment (s) received and/or (the type and severity) of the (comorbid) symptoms of trauma-related and personality disorders.

**Fig. 1 Fig1:**
[figure not shown]
A diagnostic model for the spectrum of trauma-related disorders and personality disorders. This two-dimensional diagnostic model accounts for the influence of trauma and neglect on the development of (a spectrum of) trauma-related disorders as well as personality disorders. The severity of trauma (based on factors such as the age of onset, how frequently it occurred, the relationship to the perpetrator, and the number of perpetrators) endured, situated on the y-axis, is assumed to be related to the severity of trauma-related disorders. Situated on the x-axis, the severity of emotional neglect (the quality of the early bond with the primary caregivers) represents the second dimension. This dimension is assumed to be related to the severity of personality disorders. The numbers (0–5) on the y-axis and the x-axis represent the severity scores on both dimensions, which ranges from no trauma or emotional neglect endured (score 0) to very severe trauma or emotional neglect (score 5). Individual patients can be ‘located’ somewhere in the two-dimensional square

The current study is a two-year follow-up of trauma-related and personality disorders in patients who sought treatment at a regular Dutch mental health care center, GGZ Friesland. The purpose is to examine the two-year course of trauma-related disorders and personality disorders, i.e. (symptomatic) improvement of the (comorbid) disorders, as well as identifying predictors of a (non-) favourable course of these symptoms. The duration of the follow-up period is based on clinical experience in treating patients with childhood trauma and neglect. Furthermore, in determining the follow-up period, we have taken several factors into account: because trauma-related disorders and personality disorder mostly run a chronic course, a short follow-up period, e.g. 6 months or 1 year, will probably not be able to show significant changes; however to minimalize non-response, the follow-up period should not be too long, while patients are more likely to have ended their therapy, have moved, changed their telephone number et cetera.

The primary research question is: what is the course of (symptoms of) trauma-related and personality disorders in a sample of patients in treatment over a follow-up period of 2 years? More specifically, what is the course of the core symptoms (PTSD, (symptoms of) dissociative disorders, (symptoms of) personality disorders affect dysregulation and general functioning) in a sample of treatment seeking adults with and without histories of early childhood trauma, i.e. before the age of 12? The second research question is: which variables predict course outcome after 2 year? More specifically, are demographic (gender, age) and clinical (dissociation, comorbidity in general, personality features) predictors of a (un) favourable course after 2 years? And to what extent is course outcome dependent on the type or duration of treatment (e.g., inpatient, outpatient, pharmacotherapy, psychological treatment)? The specific variables and (possible) predictors are described more extensively in the method.

Based on the theoretical model of Draijer [23, 24] and results of previous studies, we expect that type and severity of personality pathology and trauma-related pathology at baseline predict the size of improvement at follow-up, with severe (comorbid) pathology predicting less improvement than light to medium (comorbid) pathology. Furthermore, we expect that type and severity of reported trauma and neglect as well as the number of reported traumatic experiences predict the level of improvement in symptoms of trauma-related or personality disorders between baseline and follow-up. Also, we expect that level of improvement in symptoms of trauma-related or personality disorders correlates with the level of improvement of other more general psychopathology, like anxiety, depression, and general functioning. Finally, we expect that dose (amount) and type of treatment can be identified as predictors of the course of symptoms of trauma-related and personality disorders.

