## Methods/design

The design of this study is a naturalistic two-year follow-up of patients admitted to the trauma treatment program and the personality disorder treatment program at GGZ Friesland, the Netherlands. The study is supervised by the Department of Psychiatry, Vrije University Medical Center, Amsterdam, the Netherlands, experts in cohort studies.

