### Participants

Patients who sought treatment at GGZ Friesland for either personality disorders or trauma-related disorders were recruited for the baseline data collection. Baseline data were collected between November 2011 and March 2014. The inclusion period of the follow-up assessment runs from February 2014 until August 2016. All patients who completed baseline assessment will be invited to participate in the follow-up study, 2 years after they completed the baseline assessment. This includes 150 patients (116 women and 34 men): 49 patients who sought treatment for traumatic experiences and were admitted to a specialized trauma-related disorders treatment program, aimed specifically at adult survivors of prolonged early childhood trauma, and 101 patients who sought treatment for personality pathology and were consecutively referred to a specialized personality disorders treatment program. For a detailed description of the inclusion at baseline, we refer to [23]. Only participants with insufficient mastery of the Dutch language were excluded. Data on non-response as well as representativeness of the baseline sample are presented elsewhere [23]. The baseline sample was considered to represent the two relevant clinical populations.

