We overcome limitations of previous studies, as discussed above, by using structured clinical interviews as well as symptom questionnaires, carefully registering onset and type of trauma (at baseline and follow-up) and collecting several data, which potentially act as predictors of course of disorders and symptoms. Furthermore, to keep track of factors that may affect symptom change, we enumerate use of medication, received therapy (in- and outside GGZ Friesland) and traumatic experiences in the two-year period after baseline assessment. Also, we keep track of developments, like changes in offered therapies in the specialized treatment programs (of trauma-related and personality disorders) at GGZ Friesland. However, we cannot overcome some limitations, inherent in this type of research, like the use of retrospective data. Also, in addition to the clinical interviews, we use some self-report questionnaires.

An important strength of this study is that it is unique in the elaborate way in which traumatization and (personality) pathology are investigated [23]. This study will provide insight in the relation between symptoms of trauma-related disorders and personality disorders and how they affect each other in the course of treatment, while they are frequently treated as separate conditions nowadays. Identifying factors, which influence the course of the trauma-related and personality disorders, allows making predictions about the future course and offers indicators for treatment. Furthermore, the study can contribute to improve diagnosing trauma-related disorders and personality disorders as well as provide knowledge of prognostic variables that may allow the prognosis of an individual patient and the pre-classification/stratification of patients in outcome studies.

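### The plan asks how far outcome is dependent on treatment type or duration, but treatment is not randomised, programme follows the indication, and the specified model omits baseline symptom severity

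*Protocol article*

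**What the plan says.** All references are to the protocol article.

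- **Background, research questions.** The second research question includes: "And to what extent is course outcome dependent on the type or duration of treatment". Its examples are inpatient and outpatient care, pharmacotherapy and psychological treatment. The matching hypothesis reads: "we expect that dose (amount) and type of treatment can be identified as predictors of the course of symptoms". The same section expects severe baseline pathology to predict less improvement than light to medium pathology.
- **Methods/design.** "The design of this study is a naturalistic two-year follow-up of patients admitted to the trauma treatment program and the personality disorder treatment program". There is no random allocation.
- **Participants.** The trauma group is "49 patients who sought treatment for traumatic experiences and were admitted to a specialized trauma-related disorders treatment program", a programme "aimed specifically at adult survivors of prolonged early childhood trauma". The other 101 patients sought help for personality pathology and were referred to the personality programme.
- **Measurements.** Therapy data cover minutes of therapy, programme or department, group versus individual format, hospital days and medication.
- **Power calculation and Data analysis.** The specified logistic regression is for remission of PTSD on three predictors: duration of treatment, severity of traumatic experiences, and neglect. The number of predictors tested will depend on literature and on the data. The other regression described, on raw change scores, uses the trauma and neglect indexes and has no treatment term.
- **Discussion.** The issues raised are non-response, use of the same assessors, retrospective data and self-report. Treatment received is recorded as a factor that may affect change. Identifying the factors that influence course "allows making predictions about the future course and offers indicators for treatment"; the abstract says that identifying predictors "will allow to differentiate clinical profiles and will offer indicators for treatment".

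**The concern.** Asking how far outcome depends on treatment invites a causal reading. In a naturalistic cohort, a treatment variable carries with it the reasons why the treatment was given. Here the article supplies both links for programme: presenting problem and trauma history lead to programme, and trauma, neglect and baseline severity are expected to lead to poorer improvement. If those hypotheses are right, programme will be associated with outcome even if it does nothing.

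The point also bears on the model that is written down. Duration of treatment is in it, while baseline symptom severity, which the article itself expects to predict improvement, is not. If more severely ill patients are treated for longer, the duration coefficient will absorb part of the effect of severity.

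At stake is interpretation. A poorer course with longer or more intensive treatment could be reported as outcome depending on treatment when it reflects who received it.

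**Working it through.** **1. The article's own sample size.** Inputs from the Power calculation: ten events per variable, three predictors, remission 25%–75%, drop-out 20%.
- Observations per predictor: 10 / 0.25 = 40.
- Analysed: 3 × 40 = 120. Baseline: 120 / (1 − 0.20) = 150. Both figures reproduce.
- Limiting events in 120 patients at 25% or 75% remission: 120 × 0.25 = 30, so 30 / 10 = 3 predictors. All three places are taken by duration, trauma severity and neglect.

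**2. How a null treatment can look harmful (all inputs assumed).** Let remission be 60% in milder and 30% in more severe patients whatever the treatment. Let 70% of those receiving A and 30% of those receiving B be severe.
- A: 0.7 × 0.30 + 0.3 × 0.60 = 0.39.
- B: 0.3 × 0.30 + 0.7 × 0.60 = 0.51.
- Crude odds ratio: (0.39/0.61) / (0.51/0.49) = 0.61, with a true value of 1.
- Within each severity stratum the rates are equal (60% v 60%, 30% v 30%), so adjustment for severity recovers 1. This is why baseline severity belongs in the model.

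**3. Programme (remission split assumed, across the article's 25%–75% range).** Followed patients: 49 × 0.8 ≈ 39 and 101 × 0.8 ≈ 81. Suppose programme has no effect and remission differs only by presenting problem. The last column is for an unadjusted two-sided comparison.

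| Remission by presenting problem | Apparent odds ratio | Chance of p < 0.05 |
|---|---|---|
| 25% v 35% | (0.35/0.65)/(0.25/0.75) = 1.6 | about 19% |
| 25% v 50% | (0.50/0.50)/(0.25/0.75) = 3.0 | about 76% |
| 25% v 75% | (0.75/0.25)/(0.25/0.75) = 9.0 | over 99% |

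Because presenting problem nearly coincides with programme, covariates cannot separate the two here, and more patients would not help.

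**4. What the sample can carry.**
- Adding baseline severity and programme to the existing three predictors makes five: 5 × 40 = 200 analysed, 200 / 0.8 = 250 at baseline. At 50% remission, 120 × 0.5 / 10 = 6 predictors would fit, but the article plans for 25%–75%.
- One treatment term plus baseline severity plus programme makes three, which fits 120.
- Separate models within the trauma programme: 39 × 0.25 ≈ 10 to 39 × 0.50 ≈ 20 limiting events, so one or two predictors. A treatment term with two covariates does not fit.

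**The case against.** The best defence is that the framing is predictive. The sentence sits under the question of which variables predict outcome, the hypothesis speaks of predictors, and the design is openly called naturalistic. Covariate sets are commonly left to a full protocol or analysis plan that is not shown. Treatment type is not in the specified model, so no unadjusted analysis of type is actually laid down. Trauma severity and neglect are in that model, so part of the confounding is already addressed.

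Much of this stands, and it rules out several stronger readings that a reader might infer:
- *That inpatient care and medication were given because of severity.* The article says only that they are recorded. The inference is reasonable in a naturalistic design but is not documented. The same goes for duration.
- *That the article promises to choose treatments from a treatment-type coefficient.* In the abstract and the Discussion, the indicators are tied to predictors of course in general.
- *That personality-programme patients have little trauma.* No overlap figure is given, and the abstract calls both groups of disorders prevalent in survivors of chronic childhood trauma.
- *That nothing is adjusted for.* Trauma severity and neglect are.

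The defence does not cover the wording of the question itself, the absence of baseline symptom severity from a model that does contain treatment duration, or a limitations discussion that passes over confounding by indication. A later analysis plan could add covariates, but it could not make programme and presenting problem separable.

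**Conclusion.** The point holds in a limited form. The treatment question is worded more strongly than this design can support, and the specified model leaves out a prognostic factor that the article itself names. It should be changed before analysis. It does not undermine the description of the two-year course or the use of baseline variables as prognostic factors.

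The link from indication to treatment is documented for programme only. The size is unknown: the odds ratio of 0.61 and the range 1.6 to 9.0 rest on assumed remission rates and case mix, and they show what is possible rather than what is expected. The count of three permitted predictors takes the article's 120 patients and 25%–75% remission at face value.

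**What to change.** 1. In the Background question, replace *dependent on* with *associated with* for both type and duration of treatment.
2. Analyse treatment variables in the pooled sample, one treatment term at a time. Use as covariates the baseline severity of the outcome concerned (CAPS score, or number of personality disorder criteria) and programme. Keep each treatment variable to a single term so that the model stays at three predictors. Do not fit separate within-programme models.
3. Do not present the programme contrast as a comparison of treatments.
4. Name confounding by indication as a limitation in the Discussion, and say that adjustment for baseline severity reduces it without removing it.
5. In the abstract and the Discussion, limit the indicators for treatment to prognosis under care as given.

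The cost is small. The covariates are already collected and the rest is wording. The price is a narrower claim and somewhat wider intervals. Several single-term models also mean more tests under the planned Bonferroni correction, so the list of treatment terms should be short and fixed in advance.
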